## Methods and analysis

### Research subject

The study subjects were infants and children aged 0–3 years and their mothers, and the Xiamen Children's Brain Development Cohort recruited the study subjects from the society (kindergartens, elementary schools, and other institutions) and the neonatal department of Xiamen Children's Hospital. Based on the information of the mothers' pregnancy—related medical history, infants whose mothers had high inflammatory indices during pregnancy (e.g., CRP, interleukin−1β, interleukin−6, interleukin−10, and macrophage inflammatory factor−1β), or had chorioamnionitis, pathologic abnormalities of the placenta, preterm premature rupture of the membranes, or had combined gestational hypertension and diabetes mellitus with maternal inflammatory diseases were included in the observation group. Infants without maternal inflammation were the control group.

Characteristics of our included subjects included:(1) age 0–3 years;(2) gestational age 37–42 weeks;(3) birth weight >2.5 kg; and(4) no significant birth complications. Characteristics of excluded subjects included:(1) history of resuscitation from asphyxia at birth;(2) congenital structural anomalies;(3) presence of inborn inherited metabolic disorders such as phenylketonuria, galactosemia, and congenital hypothyroidism;(4) presence of a major medical condition affecting growth, or development; and(5) contraindications to magnetic resonance imaging (MRI).

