##### Mapping of brain development atlas

Based on the preprocessed MRI and EEG data, we use FreeSurfer to quantify the volumes of brain regions such as the hippocampus and prefrontal cortex, and calculate the normal range of brain region volumes related to age. Calculate and plot the curves of the volumes of specific brain regions of children by gender through non-linear functions as they change with age, and identify the critical windows of development for specific brain regions in infants. Extract time-frequency features such as α/β wave power from EEG data, construct a functional connectivity matrix, and analyze the development pattern of the resting-state EEG network through graph theory analysis and independent component analysis. Use canonical correlation analysis to explore the coordinated development relationship between the volume of MRI brain regions and the functional connectivity of EEG. At the same time, conduct piecewise regression on longitudinal data, detect the mutation points of the brain development rate, and verify its correlation with the development scores in terms of intelligence, cognition, and behavior, so as to comprehensively depict the dynamic development trajectory of brain structure and function.

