##### The impact of family environment and parenting patterns on brain development

Regarding the secondary research results, we will conduct a comprehensive analysis from two aspects: the exposure of adverse factors in mothers during pregnancy and the family environment and parenting patterns after birth. For maternal exposure to adverse factors during pregnancy, on the one hand, regarding the correlation between inflammatory indicators and brain development, we will conduct correlation analysis between brain indicators such as MRI-derived brain volume, cortical thickness, and EEG power spectral density, and the levels of inflammatory cytokines such as C-reactive protein (CRP) and Interleukin-6 (IL-6). Group children according to the inflammatory levels and compare their brain imaging, electrophysiological data, and scores of relevant abilities of children. On the other hand, for other adverse conditions during pregnancy, conduct regression analysis to explore the potential links with the future development of children. In the analysis of family factors after birth, first conduct correlation and regression analysis between the scores of the quantified family parenting scale and brain indicators such as MRI-derived brain volume, cortical thickness, and EEG power spectral density. At the same time, explore the pathways through which parenting patterns affect children's intellectual development through mediation analysis. In addition, associate family environment variables with children's emotional regulation indicators, and compare the differences in children's cognitive development under different parenting styles.

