### Strength

(1) High-standard medical services and resources: As an affiliated hospital of Fudan University and a national children's regional medical center, Xiamen Children's Hospital has advanced medical facilities and standardized medical procedures, which ensure the quality and consistency of the medical data collected. In such an environment, the reliability and accuracy of the results are greatly guaranteed. (2) High compliance with follow-up: A team of professional doctors and nurses is responsible for follow-up, which can significantly improve participant compliance. This professional follow-up not only reduces missing data, but also improves the quality and accuracy of data collection. (3) Scientific instrumentation ensures data quality: Critical medical data, such as MRI scans and exome sequencing, are done in a tightly controlled hospital laboratory environment, which avoids the recall bias that comes with questionnaires. (4) Continuous and comprehensive data collection: This cohort is designed at Xiamen Children's Hospital, which can systematically collect children's comprehensive medical data for a long time, including physical examination, treatment records and follow-up information. This mode of data collection provides a solid foundation for research. (5) Lack of selection bias: Due to the specificity of the child population, there is no specific disease in the cohort population, so data collection is not affected by the selection bias that is common in adult cohorts.

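### Maternal inflammation is to be compared with no stated adjustment although exposure already differs by sex, and the normal ranges are not limited to unexposed children

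*Protocol article*

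**What the plan says.** All references are to the protocol article.

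- **Inflammation analysis** (Data analysis, The impact of family environment and parenting patterns on brain development). For CRP and IL-6, "we will conduct correlation analysis between brain indicators such as MRI-derived brain volume, cortical thickness, and EEG power spectral density" and the cytokine levels is planned, followed by: "Group children according to the inflammatory levels and compare their brain imaging, electrophysiological data, and scores of relevant abilities of children". Regression appears in the next sentence, for a different set of exposures: "for other adverse conditions during pregnancy, conduct regression analysis to explore the potential links with the future development of children". No covariates are named for any of these.
- **Sex and gestation** (Data analysis, Cohort and data objectives). Chi-square tests and analysis of variance across subgroups such as sex and gestational age are said to secure a balanced cohort.
- **Normal ranges** (Data analysis, Mapping of brain development atlas). The plan is to "calculate the normal range of brain region volumes related to age" and "Calculate and plot the curves of the volumes of specific brain regions of children by gender through non-linear functions as they change with age". No reference population is stated. Sample size sets inflammatory and normal mothers at 1:1.
- **Recruitment** (Research subject). Children come from the community ("kindergartens, elementary schools, and other institutions") and from a hospital neonatal department. The observation group is selected on maternal inflammatory markers and conditions, including chorioamnionitis and preterm rupture of membranes. Gestational age is to be 37 to 42 weeks.
- **Enrolled so far** (Preliminary results, Table 4). Of 360 children, 187 (51.9%) are exposed and 163 (45.3%) were born at term. Mean gestation is 35.67 weeks.
- **Strength (5)**: "Lack of selection bias: Due to the specificity of the child population, there is no specific disease in the cohort population".

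**The concern.** This is an observational contrast, so any factor that differs between exposed and unexposed children and also affects the outcome will show up as an inflammation effect unless the analysis deals with it. The article chooses correlation and simple group comparison for inflammation while naming regression for other pregnancy conditions and for family factors, so the unadjusted form is what is written for this exposure. A baseline test does not remove a difference, and a non-significant one does not show balance. Table 4 compares boys with girls, not exposed with unexposed, so the balance that matters is not displayed.

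The normal ranges belong to a primary outcome. If about half the reference children are exposed, any effect of exposure is partly built into what counts as normal, and the range loses power to detect the abnormality under study.

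**Working it through.** **1. Reproducing Table 4.** Inflammation by sex is 94/203 boys and 93/157 girls. The chi-square with continuity correction is 360 × (|94×64 − 109×93| − 180)² / (203×157×187×173) = 360 × 3941² / 1,031,058,721 = 5.42, p = 0.0199 (stated 0.020). The same test on term birth (102/203 against 61/157) gives p = 0.0407 (stated 0.041).

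**2. Sex imbalance by exposure group.** The exposed are 94/187 = 50.3% boys. The unexposed are (203 − 94)/(360 − 187) = 109/173 = 63.0% boys. The gap is 12.7 percentage points.

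**3. Bias in the unadjusted contrast.** Bias = gap × sex effect in SD. The documents give no sex effect; 0.5 to 1.0 SD is assumed for a brain volume.
- 0.1274 × 0.5 = 0.064 SD
- 0.1274 × 1.0 = 0.127 SD

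**4. False-positive rate with no true effect.** For a two-sided 5% test, the rate is P(Z > 1.96 − b/SE) + P(Z < −1.96 − b/SE), with SE = √(1/n₁ + 1/n₂) in SD units. The larger scenario takes the stated 1,603 per group and assumes that the same sex gap persists.

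| Groups | SE | b = 0.064 | b = 0.127 |
|---|---|---|---|
| 187 vs 173 | 0.1055 | b/SE 0.60, 9% | b/SE 1.21, 23% |
| 1,603 vs 1,603 | 0.0353 | b/SE 1.80, 44% | b/SE 3.61, 95% |

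The bias does not shrink with sample size, so a larger study is more likely to report it as an effect.

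**5. Gestation and source.** Neither is tabulated by exposure. If the preterm share differs by 10 to 30 points and preterm birth shifts the outcome by 0.3 to 1.0 SD (both assumed), the bias is 0.10 × 0.3 = 0.03 to 0.30 × 1.0 = 0.30 SD. This shows a possible scale only.

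**6. Normal ranges from a 1:1 mixture.** Set the unexposed at mean 0, SD 1, and the exposed 0.5 SD lower (assumed). The pooled 5th centile c solves 0.5Φ(c) + 0.5Φ(c + 0.5) = 0.05, so c = −1.95. The share of exposed children below it is Φ(−1.95 + 0.5) = 7.4%. Against an unexposed reference, the cut is −1.645 and the share is Φ(−1.145) = 12.6%. With a shift of 0.25 SD (c = −1.78) the figures are 6.3% against 8.2%; with 0.75 SD (c = −2.13), 8.3% against 18.5%.

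**7. Eligibility against enrolment.** 360 − 163 = 197, and 197/360 = 54.7% were not born at term, although Research subject requires 37 to 42 weeks.

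**The case against.** The strongest reply is that the article is silent rather than wrong. It never says that the comparison is unadjusted or that the normal ranges use the whole cohort, and covariate lists and reference samples are commonly left to a fuller document. Inflammation is also not confined to correlations and group comparisons. The gene–environment section specifies a generalized linear model with CRP, IL-6 and environmental exposures, and some conditions that define the exposed group reappear among those analysed by regression. The quoted comparison concerns a secondary outcome.

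Much of this is fair, and it limits the point. It does not remove the choice of method written for the inflammation contrast, the mistaken claim about what baseline tests achieve, or the sex imbalance in the study's own table. The generalized linear model addresses gene interaction and names neither sex nor gestation.

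A reader might also infer more than the documents support:

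- *That sex differences will pass as normal development.* They will not, because the curves are drawn separately by sex.
- *That gestation and source are known to bias the contrast.* They may, but neither is tabulated by exposure. Mean gestation does not differ clearly by sex (p = 0.332), although term birth does.
- *That* "conduct piecewise regression on longitudinal data" *makes break-points look too precise.* With 11,256/3,216 = 3.5 visits per child and an assumed within-child correlation ρ of 0.5 to 0.8, √(1 + 2.5ρ) = 1.5 to 1.7. That factor applies to between-child contrasts such as exposure. Age varies within child: computed on the Table 1 schedule with the same ρ and fixed breaks between 3.5 and 24.5 months, the ratio of true to naive standard error for the change in slope is 0.69 to 1.20. The error can go either way.
- *That gestation dominates the age scale.* Among the newborn scans, gestation carries 3.88²/(3.88² + 3.30²) = 58% of the variance in postmenstrual age, if it is uncorrelated with time since birth. Over the planned 0 to 36 months, visit age has an SD of 8.6 months (about 37 weeks), and the share falls to 3.88²/(3.88² + 37²) = about 1%.

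**Conclusion.** The point holds in this form. As written, the inflammation comparison is open to confounding by sex, which already differs between exposure groups. The bias is 0.06 to 0.13 SD if sex shifts the outcome by 0.5 to 1.0 SD. The resulting false-positive rate is 9% to 23% at the present size, and 44% to 95% at 1,603 per group if the imbalance persists. Gestation and recruitment source may add to this, by an amount that the documents do not let anyone estimate.

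The normal ranges lack a stated restriction to unexposed children in a cohort that is 1:1 by plan and 51.9% exposed so far. Under an assumed 0.5 SD deficit, pooling cuts detection among the exposed at the 5th centile from 12.6% to 7.4%.

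Three statements are wrong or in conflict whatever a fuller plan contains: that baseline tests secure balance; that gestation is 37 to 42 weeks, when 54.7% of those enrolled were not term; and that selection bias is absent, when children come from two sources and are selected on maternal disease. The change should be made, but nothing here shows that the study cannot answer its question.

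**What to change.** 1. Analyse inflammation (marker level or exposure group) by regression, or by a mixed model with a child-level random effect where visits repeat. Adjust for age at visit (corrected for gestation in early infancy), sex, recruitment source and family background. Report results with and without gestational age at birth, because it may lie on the pathway from inflammation to outcome.
2. Derive the normal ranges from unexposed, term-born children and overlay the exposed.
3. Tabulate baseline characteristics by exposure group, including gestation and recruitment source.
4. Reword the Cohort and data objectives sentence to say that baseline tests describe differences, and that adjustment deals with them.
5. Reconcile the gestational-age criterion in Research subject with the enrolled sample in Table 4.
6. Delete or correct Strength (5).

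The cost is mainly wording. Sex, gestation, age at scan and exposure are in Table 4, and family background is in the questionnaires. Recruitment source is not listed in Table 2 but should be recoverable from enrolment records. The normal ranges will rest on fewer children, and intervals will be somewhat wider.

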## Preliminary results

Between December 2021 and May 2024, 360 pairs of pregnant women and their offspring were recruited into the Xiamen Childhood Brain Development Cohort, which investigated basic family information through a baseline questionnaire, children's births through medical information, and MRI scans of children's brains who entered the cohort. Of the 360 children enrolled in the study (Table 4) , 203 (56.39%) were males, the mean gestational week of the mother's pregnancy was 35.67 weeks, the mean age of the children at MRI was 3.28 weeks, and there were a total of 163 (45.3%) children born at term and 156 (43.3%) children born by normal delivery.

**Table 4 T4:** Baseline characteristics and risk factors of research subjects.

**Variable**	**Sum mean (sd)**	**Male mean (sd)**	**Female mean (sd)**	** *p* **
People (%)	360	203 (56.39)	157 (43.61)	
Gestational age (week)	35.67 (3.88)	35.85 (4.03)	35.45 (3.68)	0.332
Age at scanning (week)	3.28 (3.30)	3.25 (3.49)	3.31 (3.05)	0.849
Full-term infant (%)	163 (45.3)	102 (50.2)	61 (38.9)	0.041
Birth weight (g)	2.49 (0.87)	2.58 (0.87)	2.37 (0.85)	0.024
Vaginal delivery (%)	156 (43.3)	97 (47.8)	59 (37.6)	0.067
Parity (%)				0.141
0	55 (15.3)	30 (14.8)	25 (15.9)	
1	163 (45.3)	84 (41.4)	79 (50.3)	
≥2	142 (39.4)	89 (43.8)	53 (33.8)	
Chorioamnionitis (%)	7 (1.9)	4 (2.0)	3 (1.9)	1.000
Gestational hypertension (%)	40 (11.1)	18 (8.9)	22 (14.0)	0.170
Gestational diabetes (%)	76 (21.1)	38 (18.7)	38 (24.2)	0.257
Pathological placental abnormalities (%)	7 (1.9)	2 (1.0)	5 (3.2)	0.265
Premature rupture of membranes (%)	47 (13.1)	25 (12.3)	22 (14.0)	0.752
Eclampsia (%)	27 (7.5)	13 (6.4)	14 (8.9)	0.486
Sexually transmitted diseases (%)	28 (7.8)	15 (7.4)	13 (8.3)	0.909
Antibiotic treatment (%)	68 (18.9)	34 (16.7)	34 (21.7)	0.297
Maternal inflammatory (%)	187 (51.9)	94 (46.3)	93 (59.2)	0.020

## Discussion

The aim of this study is to establish a cohort for evaluating the brain development of infants aged 0-3 years (Figure 2). It involves collecting MRI, EEG, and other data in the early life of infants. Through image segmentation, feature extraction, and functional connectivity analysis techniques, it aims to depict the early development trajectories of brain structure, function, and infant brain development. Meanwhile, environmental risk factors in the early life of infants that affect brain development will be identified. Results from whole-exome sequencing will be integrated to analyze which genes play a crucial role in the early brain development of children. In addition, analyses will be conducted to explore how genes interact with environmental risk factors and influence the structural and functional development of infants' brains. Deep-learning algorithms will be employed to develop an early-risk assessment model for infant brain development, enabling individualized comprehensive assessments and predictions of brain intelligence.

**Figure 2 F2:**
[figure not shown]
Technology roadmap for the full research program.

### Construction of high-precision brain function map

This study will construct a map of brain function and structure from birth to early childhood and capture the dynamic changes in brain structure and function through multimodal neuroimaging techniques, including MRI and EEG. MRI will be particularly useful for visualizing structural changes, while EEG will provide insights into functional connectivity and electrical activity. Time series analysis methods will be applied, processing sequential imaging data collected from birth to early childhood to reveal key time nodes and developmental pathways in brain development. We will develop and optimize image processing algorithms, specifically for the particularity and complexity of infant brain imaging data, to ensure the accuracy and effectiveness of data analysis.

### A comprehensive analysis of the interaction between genes and the environment

In addition, the aim of this study is to analyze in depth the association between maternal inflammation and the risk of early brain development in infants and the role of genetic factors in this association, as well as to explore the risk factors for child neurodevelopment. The study will utilize whole exome sequencing technologies combined with detailed data on children's exposures (including maternal inflammation during pregnancy, nutrition, home environment, social interactions, exposome data, etc.) to analyze the interaction between genetic and environmental factors through statistical modeling. In the process, genetic information and environmental data will be integrated and analyzed, and the impact of environmental factors will be assessed to provide a comprehensive understanding of how environmental exposures during pregnancy and genetic information influence early childhood neurodevelopment.

### Early risk assessment and prediction model development

This part of the study aims to develop a comprehensive predictive model for early brain developmental disorders, based on multi-source data from neuroimaging, genetics, environmental exposures, etc. Machine learning and artificial intelligence technologies (such as deep learning, support vector machines, etc.) are applied to analyze this data and build predictive models for early risk assessment (Figure 3). Finally, based on these models, an easy-to-use personalized risk assessment tool will be developed to provide clinicians and researchers with precise early intervention and diagnostic support.

**Figure 3 F3:**
[figure not shown]
Deep learning model for early risk assessment of infant brain development.

### Strength

(1) High-standard medical services and resources: As an affiliated hospital of Fudan University and a national children's regional medical center, Xiamen Children's Hospital has advanced medical facilities and standardized medical procedures, which ensure the quality and consistency of the medical data collected. In such an environment, the reliability and accuracy of the results are greatly guaranteed. (2) High compliance with follow-up: A team of professional doctors and nurses is responsible for follow-up, which can significantly improve participant compliance. This professional follow-up not only reduces missing data, but also improves the quality and accuracy of data collection. (3) Scientific instrumentation ensures data quality: Critical medical data, such as MRI scans and exome sequencing, are done in a tightly controlled hospital laboratory environment, which avoids the recall bias that comes with questionnaires. (4) Continuous and comprehensive data collection: This cohort is designed at Xiamen Children's Hospital, which can systematically collect children's comprehensive medical data for a long time, including physical examination, treatment records and follow-up information. This mode of data collection provides a solid foundation for research. (5) Lack of selection bias: Due to the specificity of the child population, there is no specific disease in the cohort population, so data collection is not affected by the selection bias that is common in adult cohorts.

### Weakness

(1) Limited extrapolation of the population: Due to the ethnic distribution of the Xiamen population, the main enrolled population consists of Han children, and the results may not be representative of ethnic minorities. This may limit the applicability of the findings to a wider population. (2) Participant loss: A common problem in cohort studies is participant loss over time, and this study cannot avoid loss to follow-up due to moving out.
